#### Analysis of quantitative data from the general faculty (Aim 2).

Our analytical approach for general faculty targets will leverage their larger population sizes across universities (Table 1). We will use difference-in-difference (DD) models to assess the effects of being in the HIS group versus being in the LIS group on changes among faculty in norms about sexual violence and awareness of sexual violence as a problem, operationalized using identified scales (Table 5). We will use pre-post implementation data in project Years 1 and 3 to assess short-term effects of exposure to HIS versus LIS on faculty knowledge and attitudes about sexual violence and pre-post implementation data in project Years 1 and 5 to assess longer-term effects of exposure to HIS versus LIS on these outcomes. A basic DD model for our study would take the following form: Y_ijt_ = α_j_ + βP_t_ + γHIS_ij_ + δHIS_ij_*P_t_ + ε_ijt_, where Y_ijt_ is the value of the outcome observed for person i in university j at time t, HIS_ij_ is an indicator of person i in university j being in the HIS (treatment) group (HIS_ij_=1) versus the LIS (comparison) group (HIS_ij_=0), and P reflects the time period (pre=0 vs post=1 implementation of GlobalConsent). The parameter δ is the DD estimator; the point estimate of δ from this model is equivalent to a non-parametric approach that takes the difference in the changes over time between the two implementation strategies groups.

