#### University faculty (Aim 2).

All fulltime, permanent lecturers who are currently working (not on extended leave) and not in the leader or implementation team samples at the time of the baseline faculty survey will be eligible to participate. The list of eligible lecturers will be refreshed before each survey wave to ensure that all eligible lecturers are included at each wave.

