#### Survey-based data collection (Aim 1 checklist; Aims 2–3).

Survey-based data from all target populations will be collected via REDCap [49], a HIPAA-compliant, web-based data system that allows for the secure collection, transfer, storage, and analysis of study data. Customized surveys will be piloted with individuals like the focal populations but at non-study universities to gauge acceptability, inform final revisions, and assess timings to minimize respondent burden (e.g., 10–15 minutes for each leader, faculty, and implementation team survey; 16 minutes for each student survey). The survey implementation protocol described, above, under “Recruitment” will be followed for at each survey wave for faculty, implementation teams, and students to maximize their participation at baseline (~80%) and retention at endline (~90%), based on prior experience surveying students in Vietnam [51].

Measurement time points will vary for each target sample, according to the project timeline (Figure 2). Leaders will be assessed twice, once before and once after implementation. Implementation teams will be assessed quantitatively at four time points: once before the start of any implementation activities, and once immediately before, during, and after implementation of GlobalConsent. Other data on the implementation will come from administrative records collected by the IT company that is responsible for delivering GlobalConsent. Faculty will complete one assessment before implementation (Year 1) and two after the planned 12-week delivery period of GlobalConsent (Years 3, 5). Three surveys will be administered to students at six-month intervals before the planned 12-week delivery period of GlobalConsent, and three six-monthly surveys will be administered at the same interval after implementation, for a total of six assessments. At each occasion, we will send to students’ smartphones an encrypted link to a REDCap survey with ~189 questions measuring two primary behavioral outcomes and seven cognitive/knowledge, attitudinal/belief, affective, and capacity-related secondary outcomes validated in the efficacy trial [33, 50, 51] (Table 6). Secondary outcomes that are included align with our theory of change (Figure 1) and showed evidence of mediation in the trial [50]. A short modification checklist of 5–10 questions will be administered at the end of each GlobalConsent program module to understand participants’ engagement and satisfaction with the module (Table 4).

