#### Statistical power for analyses of faculty data (Aim 2).

We estimated the power to test the DD models that tested for differences in the knowledge of sexual violence legality and harm between LIS and HIS groups. Using estimates for the mean score measuring the knowledge of sexual violence legality and harm in the GlobalConsent Trial [50, 51], we computed the statistical power with a linear regression model allowing a separate intercept for each university via a simulation. We used the Stata command (ipdpower, model 1, a simulations-based command that calculates power for simple linear regression modeling) to perform the simulation. With a retained sample size of ~2,543 faculty (3,532 X 0.80 participation X 0.90 retention at wave three; ~1,272 in each implementation group), a point estimate of δ of 0.12, alpha level of .05, and 5000 simulations, estimated power was .85.

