As a first step in the analysis, we will inspect pretreatment data closely to select the modeling approach that best fits the data. Given the multi-module nature of GlobalConsent and evidence from the efficacy trial [51], we expect to see immediate level changes (improvements) in all outcomes at the first post-test survey and slope changes for all outcomes, as cognitive, attitudinal, affective, and behavioral change attenuate *partially but not entirely* [51]. We expect to see greater immediate improvement and less attenuation in the HIS group than the LIS group. A basic CITS model for the frequency of men’s sexually violent behavior may take the following form: log(E(Y_ijt_)) = B_0_ + B_1_T_t_ + B_2_Z_j_ + B_3_P_t_ + B_4_T_t_*HIS_ij_ + B_5_P_t_*HIS_ij_ + v_ij_, where Y_t_ is the outcome for the i^th^ participant for the j^th^ university at time t, B_0_ is a constant term showing the average frequency of sexually violent behavior in the reference university before implementation; Z_j_ is a vector of university dummies to allow a separate intercept for each university; T_t_ is the time elapsed since study start, where t=1,…,10 quarters; B_1_ is the pre-implementation trend in the comparison (LIS) group, and Β_1_ + B_4_ is the pre-implementation trend in the HIS group; P_t_ is a vector of indicators for each post-implementation time period; B_3_ is the level change in the reference university in the post-implementation period; v_ij_ is the random effect for the i^th^ participant at university j which would allow random subject-to-subject variation in the intercepts at each university. The difference in the actual post-implementation performance from the projected post-implementation performance in the HIS group, less this same difference in the LIS group, is the estimate of HIS effects (B_5_). This formulation assumes that all universities in the HIS group share the same trend, and all universities in the LIS group share the same trend (though possibly different from the HIS trend). This assumption could be relaxed by modeling the trends as random effects. To assess whether the slope of performance changes after implementation, we may code P_t_ as a dichotomous variable that equals 0 in the pre-implementation period and 1 in the post-implementation period. The change in slope can then be estimated by adding a three-way interaction between the higher-intensity implementation indicator (HIS_ij_), post-implementation indicator (P_t_), and linear time trend (T_t_). In this formulation, P_t_ would be coded to be centered on the introduction of implementation, so B_5_ is interpreted as the immediate shift in outcomes following implementation. Inclusion of this interaction would allow implementation effects to grow or decline over time. A similar CITS model will be applied to investigate the impact of GlobalConsent on the incidents of men’s prosocial intervening behavior in the two implementation-strategies groups.

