##### University faculty analysis.

DD methods provide unbiased effect estimates if the trend over time would have been the same between the treatment (HIS) and comparison (LIS) groups in the absence of the more intense elements of HIS implementation. However, selection bias may arise if the composition of these groups changes over time, such that the faculty population at participating universities changes systematically, for example, through substantial turnover or consolidation. One approach to address this issue is to restrict the sample of faculty to those who are available across all three survey waves and study years (1, 3, 5). If high turnover risks a substantial loss of power using this approach, we will consider the use of propensity score weighting to handle this type of confounding across four groups (HIS pre, HIS post, LIS pre, LIS post) [85] Another challenge in this analysis is the cluster-randomized design, where six universities are assigned to HIS or LIS groups. We will assess the robustness of our DD findings across a range of small-sample corrections, and we will report the methods used and findings to ensure transparency and reproducibility [86, 87].

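### The faculty difference-in-difference model and its power simulation carry no within-lecturer dependence, and the first option for turnover would tie the Year 1–3 effect to Year 5 availability

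*Protocol article*

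**What the plan says.** The section on analysis of general faculty data writes the model as "Y_ijt_ = α_j_ + βP_t_ + γHIS_ij_ + δHIS_ij_*P_t_ + ε_ijt". It introduces this with "A basic DD model for our study would take the following form". Person i is indexed over time t, but there is no person term and no covariance is stated for the residual. Two contrasts are planned. For the first, "We will use pre-post implementation data in project Years 1 and 3 to assess short-term effects"; the second compares Years 1 and 5.

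The eligibility section makes the faculty sample an open cohort: "The list of eligible lecturers will be refreshed before each survey wave to ensure that all eligible lecturers are included at each wave". The data management section gives each participant one identifier across waves, so repeat respondents can be linked.

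The faculty power section takes a retained sample of about 2,543 (about 1,272 per group), δ of 0.12 and alpha of .05, and reports power of .85. It uses a command option that "calculates power for simple linear regression modeling". No SD is given.

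Under analytical challenges, the first response listed for changing composition is to "restrict the sample of faculty to those who are available across all three survey waves and study years". Propensity score weighting is considered if that costs too much power. The same paragraph names the six-university design as a challenge and promises robustness checks across small-sample corrections, which it does not name.

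Elsewhere the protocol does allow for repeated measurement. The student model has a participant effect that "would allow random subject-to-subject variation in the intercepts at each university", and the leader and implementation-team power calculation assumes a correlation of .50 between repeated measurements.

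**The concern.** A difference-in-difference estimate from linked people is a comparison of within-person changes. If the same lecturer's answers are positively correlated, treating the surveys as separate people overstates the individual-level variance of that change. The interval is then wider than it need be, and a power figure computed the same way does not describe the analysis that the linked data allow.

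The turnover option raises a different issue. Applied to the Year 1 versus Year 3 contrast, it removes lecturers who answered both surveys because of their status two years later. That status arises after randomisation and implementation. Only the higher-intensity group's faculty are engaged with the programme through town halls, so later availability or response could differ by group, though nothing in the protocol shows that it will. The option also drops the joiners whom the refreshed list brings in. The stated reason for moving away from it is loss of power, not bias.

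**Working it through.** **Sample size.** 3,532 × 0.80 × 0.90 = 2,543, or about 1,272 per group. This reproduces the protocol's figure.

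**Stated power.** With two-sided alpha of .05 (assumed) and power of .85, δ/SE must equal 1.960 + 1.036 = 2.996. The SD this implies depends on the layout, which is not stated:

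| Layout | SE of δ | SD needed for .85 |
|---|---|---|
| Four independent cells of 1,272 | SD × √(4/1,272) | 0.714 |
| Four independent cells of 636 | SD × √(4/636) | 0.505 |
| One value per person, 1,272 per group | SD × √(2/1,272) | 1.010 |

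At an assumed SD of 1, the first layout gives power of .57 and the third gives .86. The figure of .85 can be neither confirmed nor refuted.

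**Effect of leaving out the lecturer.** If everyone answers both waves, Var(δ) = 2 × SD² × (1 − ρ) × (1/1,272 + 1/1,272). The model as written, with model-based standard errors, sets ρ = 0. The ratio of written to true individual-level SE is therefore 1/√(1 − ρ), whatever the SD. The actual alpha is 2 × [1 − Φ(1.96/√(1 − ρ))]. If .85 was computed under independence, power with a correct individual-level SE is Φ(2.996/√(1 − ρ) − 1.96).

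| ρ (assumed) | SE ratio | Actual alpha of naive test | Power with correct individual-level SE |
|---|---|---|---|
| .3 | 1.20 | .019 | .95 |
| .5 | 1.41 | .006 | .99 |
| .7 | 1.83 | <.001 | >.99 |

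These ratios are upper bounds, because the refreshed list means that overlap is incomplete.

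**Simulation.** Six universities at 72% of their Table 1 lecturer counts, randomised within pairs, SD 1, ρ = .5, true δ of zero, 1,000 runs per setting. The naive model is least squares with university dummies. The person-level test compares individual changes.

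| University-by-time variance (assumed share of total) | Naive SE | Empirical SD of δ | Naive rejection | Person-level rejection |
|---|---|---|---|---|
| 0 | 0.058 | 0.042 | .008 | .050 |
| 0.5% | 0.058 | 0.101 | .258 | .423 |
| 1% | 0.058 | 0.138 | .414 | .568 |

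Without university-level drift the naive test is conservative and the person-level test is right. With even small drift both reject far too often, and the person-level test is the worse of the two.

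**What university-level inference does to power.** Take SD 0.714, ρ = .5, equal-sized universities and a university-by-time variance of 0.5% of SD². Then SE = √(4 × 0.51 × 0.5/1,272 + (4/3) × 0.005 × 0.51) = 0.065, so δ/SE = 1.85. On a t test with 4 degrees of freedom, power is about .30. With no such variance it would be about .88.

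**The three-wave restriction.** Baseline respondents number 3,532 × 0.80 = 2,826. If 0.90 retention is assumed at each of two follow-ups, 2,543 have Years 1 and 3 and 2,289 have all three. The restriction would then drop 254 usable Year 1–3 pairs, about 10%.

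**The case against.** The strongest reply is that the equation is called basic and sets out a mean structure. No independence assumption is stated, and a condensed article may leave the covariance and the standard error method to the analysis plan. The promised small-sample corrections also matter. If they are applied at university level, they absorb within-lecturer correlation, since lecturers sit within universities. In a balanced panel δ itself is the same with or without a lecturer term. All of this stands.

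A reader might therefore infer three things that the protocol does not support:

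- **That the standard errors are wrong.** The corrections are unnamed, so this is not settled. The omission taken alone makes the test conservative; it does not produce false positives.
- **That the power of .85 is wrong.** Power of .57 rests on an assumed SD of 1 and one layout. One value per person at the same SD gives .86.
- **That the three-wave restriction is the planned analysis.** It is one option, offered if composition changes. Restricting to a closed cohort is a recognised response to that problem, and one survey-contact protocol covers all faculty.

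The reply does not remove two points. The power section commits to simple linear regression for what it counts as a retained cohort, while the student and leader/team sections allow for repeated measurement. And the Year 5 condition on a Year 1–3 effect remains if the first-listed option is taken up.

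**Conclusion.** The point holds in a limited form. Neither the faculty model as written nor its power simulation contains within-lecturer dependence, although linked lecturers can be measured up to three times. With model-based standard errors, the individual-level SE of δ would be too large by at most 1.20 at ρ = .3 and 1.41 at ρ = .5, assuming full overlap. The protocol gives neither ρ nor the SD for this analysis, and the ratios exclude university-by-time variation. The cost is lost precision, plus a power figure that cannot be checked.

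The larger threat to error rates with six universities is differential drift over time, which a lecturer term does not address. The three-wave restriction is a conditional risk of bias and lost data for the short-term contrast; its direction cannot be determined from the protocol. This is an Aim 2 analysis and does not touch the Aim 3 primary outcomes. It deserves correction because the remedy is nearly free.

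**What to change.** 1. Add a lecturer effect to the faculty model, or analyse linked change scores. Name university-level inference with a specific small-sample correction as the main basis for standard errors. Do not adopt the lecturer term alone.
2. Define the Year 1–3 sample without requiring Year 5, and the Year 1–5 sample without requiring Year 3. Keep the all-three-waves restriction as a sensitivity analysis.
3. Re-run the faculty power simulation under that same model, stating the SD, the within-lecturer correlation and the university-by-time variance assumed.

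The identifiers and data are already planned, so the cost is one model term, a few sentences and a re-run simulation. The stated power may come out less favourable once university-level variation is included.

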#### Statistical power for analyses of faculty data (Aim 2).

We estimated the power to test the DD models that tested for differences in the knowledge of sexual violence legality and harm between LIS and HIS groups. Using estimates for the mean score measuring the knowledge of sexual violence legality and harm in the GlobalConsent Trial [50, 51], we computed the statistical power with a linear regression model allowing a separate intercept for each university via a simulation. We used the Stata command (ipdpower, model 1, a simulations-based command that calculates power for simple linear regression modeling) to perform the simulation. With a retained sample size of ~2,543 faculty (3,532 X 0.80 participation X 0.90 retention at wave three; ~1,272 in each implementation group), a point estimate of δ of 0.12, alpha level of .05, and 5000 simulations, estimated power was .85.

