### Sample size {14}

Focal populations for each of these assessments include university leaders who support the GlobalConsent implementation (n=5 per university, total of 30); members of implementation teams (n≈5 per University, total≈30 members); fulltime permanent faculty at each university (estimated mean 589 per university, range 186–1038, total 3,532; based on official figures for 2021), and male student participants in GlobalConsent (estimated mean n=796 per university, range 449–1202, total=4,776 18–24 year-old, first-year undergraduate, heterosexual or bisexual men, who are attracted to women; based on official enrolment figures for 2021). We will assume 80% participation and 90% retention in each focal population.

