## Assignment of interventions: allocation

### Sequence generation {16a}

All universities in the sample are broadly matched on programs of study (health sciences) and are pair-matched on region (North, Central, South). Within matched pairs, universities will be randomized using a computer random number generator to receive ‘lower intensity’ (LIS) or ‘higher intensity’ (HIS) implementation strategies to deliver GlobalConsent to eligible undergraduate men.

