**Figure 2. F2:**
[figure not shown]
Schedule Of Enrolment, Interventions, and Assessments

**Table 1. T1:** Characteristics of Participating Universities in Vietnam

University	Founded	Region	Primary Undergraduate (UG) Programs of Study	Depts	Fulltime Lecturers (Estimate)	2021 1^st^ Year Undergrad Enrollment	2021 1^st^ Year Undergrad Men (Estimate)
1	1979	North	General/Traditional Medicine, Dentistry, Public Health, Nursing, Medical Testing, Pharmacy	72	406	1,249	625
2	1902	North	General/Traditional/Preventive Medicine, Nursing, Medical Lab. Techniques, Public Health, Ophthalmic Refraction, Nutrition	80	1,000	1,200	600
3	1957	Central	General/Traditional/Preventive Medicine, Odonto-Stomatology, Pharmacy, Nursing, Medical Testing, Medical Technology, Public Health, Midwives	30	456	1,599	800
4	1963	Central	General medicine, Pharmacy, Nursing, Medical Testing, Medical Technology, Rehabilitation, Public Health	21	186	897	449
5	1947	South	General/Traditional–Medicine, Pharmacy, Odonto-Stomatology, Nursing and Medical Technology, Public Health, Basic Sciences, Rehabilitation	7 (14/162)	1,038	2,403	1,202
6	1979	South	Medicine, Odonto-stomatolory, Pharmacy, Nursing and Medical Technology, Public Health, Basic Sciences, and Traditional Medicine	56	446	2,200	1,100
Total					3,532	9,548	4,776

Notes. Universities are numbered to protect their privacy. The figures are estimates based on 2021 data.

**Table 2 T2:** “Lower” and “Higher” Intensity Strategies to Implement GlobalConsent with Undergraduate Men, Six Universities in Vietnam

Implementation Strategies (IS), by Cluster	IS Group LIS HIS	Implementation Strategy Description	Timing	Duration	Facilitator	Barriers/Facilitators Identified in Stakeholder Interviews to be Addressed

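### The faculty power of .85 is stated for two equal arms of about 1,272, a split that no within-region allocation of the Table 1 universities can give; power is about .78 to .85 depending on the allocation

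*Protocol article*

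**What the plan says.** The section on statistical power for the faculty data (Aim 2) takes the retained sample as "3,532 X 0.80 participation X 0.90 retention at wave three", about 2,543 lecturers, and divides it into approximately "1,272 in each implementation group". With those sizes it reports "a point estimate of δ of 0.12, alpha level of .05, and 5000 simulations, estimated power was .85". The model is a linear regression with a separate intercept per university, evaluated by simulation. No standard deviation is printed.

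The Sample size section gives the faculty figures as "estimated mean 589 per university, range 186–1038, total 3,532" and adds: "We will assume 80% participation and 90% retention in each focal population". Table 1 lists the full-time lecturers of each university by region.

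The Sequence generation section says that the universities are matched in pairs on region, and then: "Within matched pairs, universities will be randomized using a computer random number generator". Lecturer numbers are not among the matching factors.

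**The concern.** The unit of allocation is the university, and each region sends one university to each arm. Arm size in lecturers is therefore whatever the three chosen universities add up to. Because the pairs are not matched on size and the Table 1 counts within each pair are very unequal, equal arms are not guaranteed and may not be possible at all.

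For a fixed total, any departure from equal arms lowers the power of a two-group comparison. A figure computed at equal arms is then the upper limit of what the design can reach at individual level, and a reader would take it as the design's power. What is at stake is the accuracy of one stated power and one stated sample split. Recruitment and conduct are not affected.

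**Working it through.** **Inputs**

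- Full-time lecturers (Table 1): North 406 and 1,000; Central 456 and 186; South 1,038 and 446. Total 3,532.
- Participation 0.80 and retention 0.90 (Sample size section), the same everywhere: 0.80 × 0.90 = 0.72.
- δ = 0.12, alpha .05, power .85 (faculty power section). Sidedness is not stated; two-sided is assumed.
- The outcome's standard deviation is not given.

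**The plan's own figures.** 3,532 × 0.72 = 2,543.04, and half of that is 1,271.5. Both sample sizes reproduce, the per-arm figure only by plain halving. Without a standard deviation, the .85 cannot be reproduced independently. It is taken as given for equal arms, which implies a non-centrality of 1.960 + 1.036 = 2.996.

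**Possible allocations.** One university per pair goes to each arm, so there are 2³ = 8 allocations and four distinct size splits:

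- 406 + 456 + 1,038 = 1,900 against 1,000 + 186 + 446 = 1,632
- 1,000 + 456 + 446 = 1,902 against 406 + 186 + 1,038 = 1,630
- 1,000 + 186 + 1,038 = 2,224 against 406 + 456 + 446 = 1,308
- 1,000 + 456 + 1,038 = 2,494 against 406 + 186 + 446 = 1,038

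**Power.** With total, effect, standard deviation and alpha fixed, the split enters only through the efficiency E = 4·n₁·n₂/(n₁ + n₂)². Power is Φ(2.996·√E − 1.960). The unknown standard deviation cancels.

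| Retained arms (× 0.72) | Allocations | E | Power |
|---|---|---|---|
| 1,368 / 1,175 | 2 of 8 | .994 | .848 |
| 1,369 / 1,174 | 2 of 8 | .994 | .848 |
| 1,601 / 942 | 2 of 8 | .933 | .825 |
| 1,796 / 747 | 2 of 8 | .830 | .779 |

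For the last row, √.830 = .911, 2.996 × .911 = 2.729, and Φ(2.729 − 1.960) = .779. The mean over the eight allocations is (4 × .848 + 2 × .825 + 2 × .779)/8 = .825.

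The nearest possible split is about 7.6% away from 1,271.5 per arm (1,368/1,271.5 = 1.076) and the furthest about 41% (747/1,271.5 = .588).

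**Cross-check.** A simulation of the difference-in-differences estimator with university intercepts (20,000 runs per split, standard deviation back-solved from .85 as about 0.71) gave .849 at equal arms. It gave .850 and .845 at the two near-equal splits, .821 at 1,601/942 and .780 at 1,796/747.

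**The case against.** The best defence reads the per-arm figure as a planning value set before randomisation. Over the eight allocations the expected retained size of each arm is exactly 1,271.5, the protocol marks the number as approximate, and the counts are 2021 estimates. As an average the figure is right. The sentence does not present it as an average, though, and power at the average split is not the average power: the latter is about .825.

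The practical effect is also modest. Half of the allocations keep about .85, and the Monte Carlo margin of 5,000 simulations (1.96 × √(.85 × .15/5,000) ≈ .01) is wider than the gap between .848 and .85. All eligible lecturers are invited, so this calculation does not set the sample size. Ordinary doubt about 80% participation is of similar size: 0.80 × .933 ≈ 75% participation would cost as much as the 1,601/942 split, and 0.80 × .830 ≈ 66% as much as the 1,796/747 split. All of this stands and keeps the point minor.

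The protocol also does not say what size each university was given in the simulation. If the real sizes were used, the .85 may already reflect them, and the sentence then misreports its inputs. It needs correcting either way.

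Three stronger readings are tempting and not supported:

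- A reader might infer that the faculty analysis has power of only .78. That is the worst case, in 2 of 8 allocations, and it is derived from the protocol's own .85.
- A reader might infer that the sponsor knows the actual split and could simply print it. The documents do not say so. Under Implementation {16c}, non-study staff at the Vietnamese partner organisation carry out the allocation. Under Who will be blinded {17a} and Data management {19}, the two US university teams learn it only after the main analyses.
- A reader might take .78 to .85 as the true power. It is an individual-level figure. With three universities per arm, university-level variation in change would matter separately, and the section on analytical challenges already acknowledges the clustered design and plans small-sample corrections.

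**Conclusion.** The point holds as a small error in a stated sample split and its power. The regional pairing and the Table 1 counts rule out two arms of about 1,272. Individual-level power is about .85 in four of the eight allocations, about .83 in two and about .78 in two, so the loss is at most about seven percentage points, to just under .80.

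This rests on four assumptions: the protocol's .85 is the equal-arm value; the test is two-sided; participation and retention are the same at every university; and the 2021 counts hold. It concerns arm imbalance only and takes the protocol's individual-level error model as given.

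**What to change.** In the faculty power section, replace the equal per-arm figure with a statement that arm sizes depend on the allocation: 747 to 1,796 retained lecturers per arm, averaging about 1,272. Restate power as about .78 to .85 depending on the allocation, and note that this is at individual level, before any university-level variation.

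Do not print the actual arm sizes before unblinding. The eight possible arm totals are all different, so sizes labelled by arm would, beside Table 1, show which universities received which bundle. The range needs no unblinding.

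The cost is one re-run of the simulation over the possible splits, an edited sentence, and a slightly less favourable stated power. Design and conduct do not change.

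### The faculty power of .85 leaves out university-level change and cluster-level degrees of freedom; with six universities randomized it is about .62 on 4 df even in the most favourable variance case.

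*Protocol article*

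**What the plan says.** The section on statistical power for analyses of faculty data (Aim 2) describes the calculation: "we computed the statistical power with a linear regression model allowing a separate intercept for each university via a simulation". It names a Stata simulation routine in its simple-linear-regression option. The outcome inputs are described only as "Using estimates for the mean score measuring the knowledge of sexual violence legality and harm in the GlobalConsent Trial"; no SD, intraclass correlation or between-wave correlation is printed. The retained sample is about 2,543 lecturers, about 1,272 per group. The result is "a point estimate of δ of 0.12, alpha level of .05, and 5000 simulations, estimated power was .85".

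The analysis model, in the section on quantitative data from the general faculty (Aim 2), has a university intercept, a period effect, an arm effect, their interaction δ, and one error term at the level of the person and time.

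Sequence generation {16a} says that universities are pair-matched on region (North, Central, South) and randomized within pairs. That makes three pairs. The university faculty paragraph under analytical challenges says "Another challenge in this analysis is the cluster-randomized design, where six universities are assigned to HIS or LIS groups", and then "We will assess the robustness of our DD findings across a range of small-sample corrections". It names no correction and no degrees of freedom.

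**The concern.** δ is a difference between arms in change over time. University intercepts take out stable differences in level, but they do not take out differences in change. If faculty norms at one university shift for local reasons, such as new leadership, a concurrent programme or staff turnover, that shift goes directly into the error of δ. Only three universities per arm are available to average it out, and more lecturers per university do not reduce it.

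Separately, even if such shifts were zero, an analysis that respects the unit of randomization must estimate its error from six universities and use a t reference with very few degrees of freedom. The described calculation contains neither element. Yet the protocol itself calls the cluster-randomized design a challenge for this same DD analysis.

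At stake is how the faculty result is read. With .85 as the stated power, a null result looks fairly informative. If the cluster-respecting test has much lower power, it is not. In the other direction, a significant result from the lecturer-level model can reflect university-level drift instead of an effect of the higher-intensity strategies.

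**Working it through.** **Inputs from the protocol.** δ = 0.12; alpha = .05 (two-sided is assumed, as sidedness is not stated); power = .85; 3,532 lecturers, 80% participation, 90% retention; six universities, three per arm, three regional pairs; lecturers per university in Table 1: 406, 1,000, 456, 186, 1,038, 446.

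**Sample size.** 3,532 × 0.80 × 0.90 = 2,543.04, and half of that is 1,271.5. This agrees with the protocol.

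**The .85 itself.** It cannot be reproduced independently, because no SD is given. It corresponds to a lecturer-level z-test if the SD is about 1.01 (two groups of 1,272 change scores), about 0.71 (four independent cells of 1,272), or about 0.50 (2,543 observations in all). The first step below does not depend on which of these was used.

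**Step 1: change only the reference distribution.**
- Signal-to-noise ratio implied by .85: z(.975) + z(.85) = 1.960 + 1.036 = 2.996.
- Implied standard error of δ: 0.12 / 2.996 = 0.0400.
- University-by-period variance is set to zero, the most favourable case.
- Power = P(T > critical value), with T non-central t and non-centrality 2.996.

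| Reference | Critical value | Power |
|---|---|---|
| Normal (as stated) | 1.960 | .85 |
| 5 df (clusters minus one) | 2.571 | .67 |
| 4 df (six universities, two arms) | 2.776 | .62 |
| 2 df (three pairs) | 4.303 | .39 |

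Rounding of .85 (.845 to .855) moves the 4-df figure only between .61 and .62.

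**Step 2: simulation check, variance in change still zero.** A t-test on university means with 4 df rejects in .62 of runs with equal university sizes and in about .51 with sizes in proportion to Table 1. The paired version on 2 df gives .39 and about .32. A CR1 cluster-robust standard error with 5 df rejects in about .70 to .80 of runs, but its type I error is about 8% to 11%.

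**Step 3: add university-level variation in change (assumed values).** Take the four-cell reading, so lecturer variance s² = 0.0400² × 1,271.5 / 4 ≈ 0.51. Let ICC be the university variance as a fraction of s², and CAC the between-wave correlation of university effects. The added variance of δ is 2 × ICC × (1 − CAC) × s² × (1/3 + 1/3).

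| ICC | CAC | SE of δ | Power, 4 df | Type I error of the uncorrected z-test |
|---|---|---|---|---|
| 0.01 | 0.9 | 0.0478 | .48 | 10% |
| 0.01 | 0.8 | 0.0544 | .39 | 15% |
| 0.05 | 0.9 | 0.0707 | .26 | 27% |
| 0.05 | 0.8 | 0.0917 | .17 | 39% |

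The last column is 2 × P(Z > 1.96 × 0.0400 / SE). ICC and CAC are assumptions; the protocol gives neither.

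**The case against.** Several points on the other side are fair.

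- A reader might infer that .62 is the most the planned analysis could achieve. The documents do not support that. No correction is named, 5 df gives .67, and a CR1 standard error rejects more often still. The last of these does so by exceeding its nominal error rate, so it is no reason to keep .85, but .62 remains the value for one particular test.
- A reader might infer that the protocol commits the faculty analysis to a corrected test that replaces the one powered. It does not. The sentence promises a robustness assessment around the DD model, and that DD model is the one powered. So the two sections do not contradict each other; the defect is that the power model leaves out clustering in change.
- It would be unfair to call the calculation a plain regression that ignores universities. It has a separate intercept for each. They address level and leave change untouched.
- The 2-df figure presumes an analysis by pair, whereas pairs appear in the protocol only in the randomization.
- The values from .48 to .17 and the inflated error rates rest on assumed inputs. With zero variation in change, power on 4 or 5 df is still better than even.
- Faculty norms belong to Aim 2, while the primary outcomes are student behaviours. All eligible lecturers are invited and the six universities are fixed, so this figure does not drive recruitment.
- The choice of a specific correction can be left to an analysis plan that is not shown.

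These points limit the wording and the weight of the concern. They do not rescue .85: the drop to .62 or .67 needs no assumed ICC.

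**Conclusion.** The point holds in this form. The stated power of .85 is a lecturer-level figure and is not the power of a faculty comparison that respects six randomized universities and holds its type I error. With university-by-period variance at zero and the signal-to-noise ratio implied by .85 unchanged, power is about .62 on 4 df, .67 on 5 df and .39 on 2 df. These rest on a two-sided alpha of .05 and equal university sizes; with Table 1 sizes the 4-df test on university means gives about .51. Any university-level variation in change reduces power further. The .48 to .17 range on 4 df illustrates how fast, under ICCs of 0.01 to 0.05 and between-wave correlations of 0.8 to 0.9, and should not be read as an estimate for this trial. The point concerns the credibility of a secondary-aim power statement and of the inference drawn from it. It does not show that the faculty result will be null or false.

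**What to change.** In the faculty power section, rerun the simulation with a university-by-period random effect, the Table 1 university sizes and cluster-level degrees of freedom. State the SD and the variance assumptions, and replace .85 with the resulting range, starting from zero university-level variation in change.

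In the university faculty paragraph under analytical challenges, say that the faculty conclusion rests on a cluster-corrected test shown to hold its type I error with six clusters, and do not treat the correction only as a robustness check on the uncorrected result. The exact method can be named in the analysis plan.

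The cost is one rerun and a less favourable stated power. No lecturers, universities or survey waves are added.
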